### Study background and flowchart

BaSICS is a large pragmatic critical trial that aims to provide evidence for or against the use of Plasma-Lyte 148 over 0.9% saline and of lower infusion speeds during fluid challenges in critically ill patients. Patients were randomized using a web-based system designed for the trial in a factorial way (blocks of 12 patients), stratified by recruiting site in a 1:1:1:1 ratio to both define a specific fluid group (Plasma-Lyte 148 or 0.9% saline) and slow (333mL/h) or rapid (999mL/h) infusion during a fluid challenge.^(1)^ The details of the inclusion and exclusion criteria have been addressed in the original protocol, together with recommendations for fluid management and safety rules.^(1)^ The planned flowcharts for both interventions are shown in figures 1 and 2, respectively. BaSICS is a large pragmatic trial, and a screening log was not obtained at each site due to the large number of included patients and for local logistics reasons.

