### Primary outcome analysis

Mortality until 90 days will be tested using mixed-effects Cox proportional hazard models, considering sites as the random variable (frailty models)^(3)^ adjusted for age, baseline SOFA^(4)^ score and the type of admission (planned admission, unplanned admission with baseline sepsis and unplanned admission without baseline sepsis). Sepsis will be defined as infection plus organ failure as per the Sepsis 3 criteria.^(2)^ Proportionality of the hazard ratio will be assessed using the Grambsch and Thernau method,^(5)^ and interactions between the intervention arms (infusion solution and speed) will be tested on this model. If the interaction parameter is significant, we intend to report only one manuscript describing “inside the table” effects, that is, exploring all the four possible combinations and their effects on mortality. If the interaction parameter is not significant at the 5% significance level, marginal effects for each group will be highlighted. In this case, “inside the table” effects shall be reported as supplementary material following CONSORT recommendations for 2 × 2 factorial designs.^(6,7)^ Kaplan-Meier curves will be presented comparing the four arms and separated considering only Plasma-Lyte® *versus* Saline, and Slow *versus* Rapid infusion. Patients with missing follow-up at 90-days will be added to the main primary outcome analysis and censored at their last known follow-up time, patients without discharge information will be imputed by chained equations method using site, age, baseline SOFA score and type of admission.

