### Secondary outcomes

The following secondary endpoint analysis were defined:

- Renal replacement therapy up to 90 days.- Acute renal failure incidence defined as Kidney Disease Improving Global Outcomes (KDIGO)^(8)^ stage 2 or 3 evaluated at days 3 and 7. We plan to use both serum creatinine and diuresis for the KDIGO classification. Diuresis was collected on a daily basis during BaSICS, and therefore we will use the average diuresis over 24 hours as the urinary output criteria in KDIGO; creatinine criteria will be used if diuresis information is not registered. In case of a disagreement between creatinine and diuresis criteria for KDIGO, we will consider the worst criteria.- SOFA score assessed both as the total value and as individual components and each of their components separately (Cardiovascular, Neurologic, Coagulation, Hepatic and Respiratory) will be evaluated on day 3 and 7.- Mechanical ventilation-free days within 28 days.

Renal replacement therapy up to 90 days will be estimated using a mixed Poisson model adjusted for age, baseline SOFA and admission type and will be reported as the incidence per 1,000 patient-days. Alternatively, we will also report renal replacement therapy at 90 days in a competing risk model considering death as a competitor for the need for RRT. Incidence of AKI at days 3 and 7 will be tested with mixed generalized linear models with a binomial distribution and the logit link function (also known as a mixed logistic regression model^(9)^) considering site as a random effect; the results will be presented with odds ratios and 95% confidence intervals. Additional analysis combining KDIGO and death will be performed as a supportive analysis to address competitive risks issues.

SOFA score will be tested with a mixed generalized linear model using the distribution that best fits the data (Poisson, gamma, inverse gaussian, or multinomial, among others), and the results will be presented as the mean and/or median differences or ratios with respective 95% confidence intervals using the delta method. Organ dysfunctions at day 3 and 7 (specific SOFA item - cardiovascular, neurologic, coagulation and respiratory as a dichotomous variable defined as higher than 2) will be tested with mixed logistic regression models.

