Total SOFA score will be missing if patients died before the measurement time point , and multiple imputation by chain equations using the *mice* R^(10)^ package shall be performed to address the competitive risk bias. Acquired SOFA trend and baseline characteristics will be considered to predict any missed SOFA scores at 3 and 7 days, with the study arms as covariates. Sensitivity analysis without the arms as covariates shall also be performed.

Mechanical ventilation-free days within 28 days will be tested considering the proportion of ventilator-free days in that time frame using zero/one inflated beta or beta-binomial regression assuming zero free-days for those patients who died within that period independently of the amount of time the patient actually used the ventilator. We will consider as ventilation day any day where the patient received any duration of mechanical ventilation. Effect measures shall be presented as the absolute mean difference.

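### The ventilator-free-days model names no site term although randomisation is stratified by site; fitted as written, its standard error is somewhat conservative

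*SAP article*

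**What the plan says.** Under Study background and flowchart, patients are randomised in blocks of 12, "stratified by recruiting site in a 1:1:1:1 ratio".

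The models for the main outcomes are then described as follows.

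- **Primary outcome:** a mixed-effects Cox model with site as a frailty term.
- **Renal replacement therapy (RRT):** a "mixed Poisson model adjusted for age, baseline SOFA and admission type". A second analysis uses a "competing risk model considering death as a competitor for the need for RRT", and no site term is named for it.
- **Acute kidney injury (AKI) at days 3 and 7:** mixed logistic regression "considering site as a random effect; the results will be presented with odds ratios and 95% confidence intervals".
- **Total SOFA:** "SOFA score will be tested with a mixed generalized linear model using the distribution that best fits the data".
- **Organ dysfunction:** mixed logistic regression, random effect not named.
- **Tertiary mortality and length of stay:** mixed models with site named.
- **Ventilator-free days within 28 days:** a model "using zero/one inflated beta or beta-binomial regression assuming zero free-days for those patients who died within that period". The article adds: "Effect measures shall be presented as the absolute mean difference".

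The ventilator-free-days text does not call the model mixed and mentions neither a random effect nor site. The general rules at the head of the planned analyses cover alpha, confidence intervals and intention to treat. They do not say that site enters every model.

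**The concern.** When allocation is blocked within site, each site contributes nearly equal numbers to each arm, so differences between sites largely cancel out of the arm contrast. An analysis that ignores site still includes those differences in the residual variance. Its standard error is then larger than the true sampling error of the contrast.

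Ventilator-free days could be exposed to this, because deaths score zero. The outcome therefore combines mortality with ventilation practice, and both can differ between units. The fluid and the speed comparison would be affected alike.

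There is also a specification issue. An analyst who follows the text literally leaves site out. One who assumes that site was meant must decide late how to enter it. In a model inflated at zero and one, site could go into the zero part, the one part, the beta part or all three. The article's introduction says that the plan exists to prevent choices of this kind once results are known.

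**Working it through.** **The plan's own figure.** The article states no power or precision for ventilator-free days. Its only power figure is 89% for the primary outcome (11,000 patients, 35% control mortality, hazard ratio 0.9). This reproduces. Treated-group mortality is 1 − 0.65^0.9 = 0.3214, events are 5,500 × (0.35 + 0.3214) = 3,693, and the Schoenfeld formula gives 89.3% at two-sided 5%. It says nothing about the present point.

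**Inputs.** Stratification by site, blocks of 12, the 5% alpha (taken as two-sided) and the total of 11,000 come from the article. The ICC is not given and is varied from 0.02 to 0.15. The 80% reference power is also an assumption.

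**Formulas.** With arms balanced within site, the true variance of the contrast is proportional to 1 − ICC, while a model without site uses the total variance. Then:

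- standard-error and interval inflation: k = 1/√(1 − ICC)
- actual two-sided error: 2 × (1 − Φ(1.96k))
- power without site, where a site-adjusted test has 80%: Φ(1.96 + 0.8416 − 1.96k)

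Example at ICC 0.10: k = 1/√0.90 = 1.054 and 1.96k = 2.066. The error is 2 × (1 − Φ(2.066)) = 3.9%, and the power is Φ(2.8016 − 2.066) = Φ(0.736) = 76.9%.

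| Assumed ICC | Interval width | Actual error at nominal 5% | Power instead of 80% |
|---|---|---|---|
| 0.02 | ×1.010 | 4.8% | 79.4% |
| 0.05 | ×1.026 | 4.4% | 78.5% |
| 0.10 | ×1.054 | 3.9% | 76.9% |
| 0.15 | ×1.085 | 3.4% | 75.0% |

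**Simulation check.** The set-up was about 11,000 patients in 75 sites (number assumed), with permuted blocks of 12 within site. Deaths scored 0, some patients scored 28, and the rest were beta-binomial. Normal site effects acted on all three parts. There were 1,500 replicates per setting. A plain difference in means was compared with a within-site difference.

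| ICC reached | Model SE, no site (null) | Empirical SE, no site (null) | Null rejection, without / with site | Power, without / with site |
|---|---|---|---|---|
| 0.02 | 0.228 | 0.228 | 5.1% / 5.3% | 56.3% / 57.1% |
| 0.07 | 0.230 | 0.226 | 4.1% / 5.1% | 55.7% / 58.3% |
| 0.14 | 0.232 | 0.215 | 2.9% / 4.1% | 48.5% / 55.7% |

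The direction agrees with the formula, and the effect disappears at low ICC.

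**One of the plan's own models.** A beta-binomial model without site was fitted in 400 null replicates at each of two ICCs. At ICC 0.14 the model SE was 0.228 against an empirical 0.217, a ratio of about 1.05. At ICC 0.07 it was 0.227 against 0.228, so no excess was seen. With 400 replicates an empirical SE has a relative error of about 1/√(2 × 400) = 3.5%, so this check is coarse. Null rejection was 4.5% and 5.0% respectively, which 400 replicates cannot separate from 5%.

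**The case against.** Several stronger readings are tempting, and the article does not support them.

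- **That the plan excludes site.** It does not say so. The ventilator-free-days text gives a choice of distribution, the handling of death and the effect measure, and is silent on site. The analysts may have intended a random effect.
- **That every other secondary model includes site.** Site is named explicitly only for AKI. For RRT, total SOFA and organ dysfunction it is inferred from the word mixed. The competing-risk analysis of RRT names no site term, and the supportive analysis of KDIGO stage or death states no model.
- **That a material loss of power is established.** The ICC and the number of sites are both assumed. A loss of five points from 80% needs an ICC of about 0.15, and nothing in the article points to that value. Large site effects imply very different sites. Around 35% mortality (logit −0.62), a site SD of 0.7 on the logit scale spans −2.02 to 0.78 at ±2 SD, or mortality of about 12% to 69%. Even an SD of 0.4 spans about 20% to 55%.
- **That ignoring site makes the test too liberal.** With allocation balanced within site, the error runs in the conservative direction.

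It can also be said that the tabulated sizes come from a formula and from a difference in means, and do not carry over exactly to the models named in the plan. That stands, and the beta-binomial check shows it. What remains is the omission itself. The article states the mixed structure for its other main models, so condensation for a journal does not readily explain its absence here.

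**Conclusion.** The point holds as a minor one. Taken as written, the ventilator-free-days analysis leaves out the stratification factor, and its standard error is somewhat conservative. There is no bias and no inflation of type I error, and the primary outcome is untouched.

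The cost in precision ranges from about 1% wider intervals and half a point of power at ICC 0.02 to about 8% and five points at ICC 0.15. It is negligible at the low end, and the beta-binomial check could not detect it at ICC 0.07. These sizes rest on an assumed ICC, near-complete balance within sites and an 80% reference power. The direction needs only the balance within sites and some between-site variation.

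**What to change.** In the ventilator-free-days paragraph under Secondary outcomes, before database lock:

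1. State that the model includes recruiting site as a random intercept, in line with the other main models. If the form inflated at zero and one is used, say that the intercept enters the zero and one parts as well as the beta part.
2. State that the absolute mean difference is obtained by standardising model predictions over sites.
3. Name a fallback in case the mixed model does not converge: the site-stratified mean difference, with within-site differences pooled by weights proportional to site size.

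This takes a sentence or two and no new data, since site is already needed for the primary model. The small downside is a heavier model with some risk of non-convergence, which the fallback covers.

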### Tertiary outcomes

We defined tertiary endpoints that should be considered exploratory:

Intensive care unit (ICU) and hospital mortality will be tested with mixed logistic regression models considering site as the random effect and adjusted for the same variables used in the primary analysis.Length of stay in the ICU and in the hospital will be compared with mixed generalized linear models with a Poisson distribution and a logarithm link, also considering site as the random intercept effect.Quality of life six months after ICU discharge will be analyzed in a 10% sample using EQ-5D-3L questionnaires.^(11)^ This will be reported separately in a different manuscript.

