### Sample size calculation, interim analyses and database lock

BaSICS was designed to enroll 11,000 patients. The sample size was calculated estimating 35% mortality within 90 days in the control group (saline and rapid infusion). This was based on data from large Brazilian cohorts, as discussed in the study protocol.^(1)^ The defined sample size allowed for an 89% power to detect a hazard ratio of 0.9 for both interventions assuming no interaction was expected among the study interventions.

Four interim analyses were performed in BaSICS. The first analysis of the first 1,000 patients aimed exclusively at checking the safety of the fluid speed comparison. Three other interim analyses followed at 25% (2,750 patients), 50% (5,500 patients) and 75% of the sample size (8,250 patients). We used very restrictive rules for stopping the trial for efficacy and we shall not adjust p-values for sequential tests (Appendix 1). A database lock will be applied after 90-day follow-up of all patients is obtained and all needed actions to obtain follow-up have been deployed. The baseline features of the included patients will be displayed as in table 1.

**Table 1 t1:** Baseline characteristics of the patients

Characteristics	Plasma Lyte		0.9% Sodium chloride	
	Slow infusion (n = xxx)	Rapid infusion (n = xxx)	Slow infusion (n = xxx)	Rapid infusion (n = xxx)
Age (years)	xx.x ± xx.x	xx.x ± xx.x	xx.x ± xx.x	xx.x ± xx.x
Female sex	xx.x (xx.x)	xx.x (xx.x)	xx.x (xx.x)	xx.x (xx.x)
Weight (kg)	xx.x ± xx.x	xx.x ± xx.x	xx.x ± xx.x	xx.x ± xx.x
Height (m)	xx.x ± xx.x	xx.x ± xx.x	xx.x ± xx.x	xx.x ± xx.x
Source of admission to ICU				
Elective surgery	xx.x (xx.x)	xx.x (xx.x)	xx.x (xx.x)	xx.x (xx.x)
Nonelective surgery	xx.x (xx.x)	xx.x (xx.x)	xx.x (xx.x)	xx.x (xx.x)
Emergency Department	xx.x (xx.x)	xx.x (xx.x)	xx.x (xx.x)	xx.x (xx.x)
Ward	xx.x (xx.x)	xx.x (xx.x)	xx.x (xx.x)	xx.x (xx.x)
Another hospital	xx.x (xx.x)	xx.x (xx.x)	xx.x (xx.x)	xx.x (xx.x)
Another ICU	xx.x (xx.x)	xx.x (xx.x)	xx.x (xx.x)	xx.x (xx.x)
APACHE II	xx.x [xx.x - xx.x]	xx.x (xx.x - xx.x]	xx.x (xx.x - xx.x]	xx.x [xx.x - xx.x]
SOFA	xx.x [xx.x - xx.x]	xx.x [xx.x - xx.x]	xx.x [xx.x - xx.x]	xx.x [xx.x - xx.x]
Mechanical ventilation				
Noninvasive mechanical ventilation > 12 hours	xx.x (xx.x)	xx.x (xx.x)	xx.x (xx.x)	xx.x (xx.x)
Invasive mechanical ventilation	xx.x (xx.x)	xx.x (xx.x)	xx.x (xx.x)	xx.x (xx.x)
Serum creatinine (mg/dL)	xx.x ± xx.x	xx.x ± xx.x	xx.x ± xx.x	xx.x ± xx.x

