### Planned statistical analysis for the primary, secondary and tertiary endpoints

All clinical endpoints shall be presented as similar as possible to those shown in table 2. Categorical variables will be presented as the number and percentage. Continuous variables will be presented as the mean and standard deviation for variables such as age and physiological parameters (blood pressure, sodium and potassium levels). We will favor the presentation of ordinal variables, such as Sequential Organ Failure Assessment (SOFA) score, as the median and interquartile range. An alpha of 5% and 95% confidence intervals will be used unless otherwise stated; similarly, all analyses will be based on the intention-to-treat principle unless otherwise stated. Analyses will be performed with the latest R version available at the end of the patients’ follow-up (most probably version 4.0).

**Table 2 t2:** Outcomes comparing slow versus fast infusion speed and Plasma-Lyte versus 0.9% sodium chloride

Characteristics	Plasma-Lyte	0.9% Sodium chloride	Effect measure	p value*	Slow infusion	Rapid infusion	Effect measure	p value†	p value‡
			(95%CI)		(n = xxx)	(n = xxx)	(95%CI)		
Primary outcome									
90-day mortality	xx.x (xx.x)	xx.x (xx.x)	x.xx (x.xx - x.xx)	x.xx	xx.x (xx.x)	xx.x (xx.x)	x.xx (x.xx - x.xx)	x.xx	x.xx
Secondary outcomes									
Acute renal failure with need for renal replacement therapy within 90 days									
Incidence (per 1000 patient-day)	xx.x	xx.x	x.xx (x.xx - x.xx)	x.xx	xx.x	xx.x	x.xx (x.xx - x.xx)	x.xx	x.xx
At day 1	xx.x (xx.x)	xx.x (xx.x)		-	xx.x (xx.x)	xx.x (xx.x)		-	-
At day 2	xx.x (xx.x)	xx.x (xx.x)		-	xx.x (xx.x)	xx.x (xx.x)		-	-
At day 3	xx.x (xx.x)	xx.x (xx.x)		-	xx.x (xx.x)	xx.x (xx.x)		-	-
At day 7	xx.x (xx.x)	xx.x (xx.x)		-	xx.x (xx.x)	xx.x (xx.x)		-	-
In hospital (at least one renal substitution in hospital stay)	xx.x (xx.x)	xx.x (xx.x)	x.xx (x.xx - x.xx)	x.xx	xx.x (xx.x)	xx.x (xx.x)	x.xx (x.xx - x.xx)	x.xx	x.xx
Unknown at 90-day follow up	xx.x (xx.x)	xx.x (xx.x)		-	xx.x (xx.x)	xx.x (xx.x)		-	-
Lost contact for 90-day follow-up	xx.x (xx.x)	xx.x (xx.x)		-	xx.x (xx.x)	xx.x (xx.x)		-	-
Incident renal failure (using KDIGO ≥ 2) at day 3	xx.x (xx.x)	xx.x (xx.x)	x.xx (x.xx - x.xx)	x.xx	xx.x (xx.x)	xx.x (xx.x)	x.xx (x.xx - x.xx)	x.xx	x.xx
KDIGO ≥ 2 or death at day 3	xx.x (xx.x)	xx.x (xx.x)	x.xx (x.xx - x.xx)	x.xx	xx.x (xx.x)	xx.x (xx.x)	x.xx (x.xx - x.xx)	x.xx	x.xx

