Incident renal failure (using KDIGO ≥ 2) at day 7	xx.x (xx.x)	xx.x (xx.x)	x.xx (x.xx - x.xx)	x.xx	xx.x (xx.x)	xx.x (xx.x)	x.xx (x.xx - x.xx)	x.xx	x.xx
KDIGO ≥ 2 or death at day 7	xx.x (xx.x)	xx.x (xx.x)	x.xx (x.xx - x.xx)	x.xx	xx.x (xx.x)	xx.x (xx.x)	x.xx (x.xx - x.xx)	x.xx	x.xx
SOFA > 2 at day 3									
Cardiovascular	xx.x (xx.x)	xx.x (xx.x)	x.xx (x.xx - x.xx)	x.xx	xx.x (xx.x)	xx.x (xx.x)	x.xx (x.xx - x.xx)	x.xx	x.xx
Neurologic	xx.x (xx.x)	xx.x (xx.x)	x.xx (x.xx - x.xx)	x.xx	xx.x (xx.x)	xx.x (xx.x)	x.xx (x.xx - x.xx)	x.xx	x.xx
Coagulation	xx.x (xx.x)	xx.x (xx.x)	x.xx (x.xx - x.xx)	x.xx	xx.x (xx.x)	xx.x (xx.x)	x.xx (x.xx - x.xx)	x.xx	x.xx
Respiratory	xx.x (xx.x)	xx.x (xx.x)	x.xx (x.xx - x.xx)	x.xx	xx.x (xx.x)	xx.x (xx.x)	x.xx (x.xx - x.xx)	x.xx	x.xx
Total SOFA score at day 3	xx [xx - xx]	xx [xx - xx]	x.xx (x.xx - x.xx)	x.xx	xx [xx - xx]	xx [xx - xx]	x.xx (x.xx - x.xx)	x.xx	x.xx
SOFA > 2 at day 7									
Cardiovascular	xx.x (xx.x)	xx.x (xx.x)	x.xx (x.xx - x.xx)	x.xx	xx.x (xx.x)	xx.x (xx.x)	x.xx (x.xx - x.xx)	x.xx	x.xx
Neurologic	xx.x (xx.x)	xx.x (xx.x)	x.xx (x.xx - x.xx)	x.xx	xx.x (xx.x)	xx.x (xx.x)	x.xx (x.xx - x.xx)	x.xx	x.xx
Coagulation	xx.x (xx.x)	xx.x (xx.x)	x.xx (x.xx - x.xx)	x.xx	xx.x (xx.x)	xx.x (xx.x)	x.xx (x.xx - x.xx)	x.xx	x.xx
Respiratory	xx.x (xx.x)	xx.x (xx.x)	x.xx (x.xx - x.xx)	x.xx	xx.x (xx.x)	xx.x (xx.x)	x.xx (x.xx - x.xx)	x.xx	x.xx
Total SOFA score at day 7	xx [xx - xx]	xx [xx - xx]	x.xx (x.xx - x.xx)	x.xx	xx [xx - xx]	xx [xx - xx]	x.xx (x.xx - x.xx)	x.xx	x.xx
Mechanical ventilation-free days within 28 days	xx [xx - xx]	xx [xx - xx]	x.xx (x.xx - x.xx)	x.xx	xx [xx - xx]	xx [xx - xx]	x.xx (x.xx - x.xx)	x.xx	x.xx
Tertiary outcomes	xx.x (xx.x)	xx.x (xx.x)	x.xx (x.xx - x.xx)	x.xx	xx.x (xx.x)	xx.x (xx.x)	x.xx (x.xx - x.xx)	x.xx	x.xx
Death in ICU									
Death in hospital	xx.x (xx.x)	xx.x (xx.x)	x.xx (x.xx - x.xx)	x.xx	xx.x (xx.x)	xx.x (xx.x)	x.xx (x.xx - x.xx)	x.xx	x.xx
Days in ICU (days)	xx.x (xx.x)	xx.x (xx.x)	x.xx (x.xx - x.xx)	x.xx	xx.x (xx.x)	xx.x (xx.x)	x.xx (x.xx - x.xx)	x.xx	x.xx
Days in hospital (days)	xx [xx - xx]	xx [xx - xx]	x.xx (x.xx - x.xx)	x.xx	xx [xx - xx]	xx [xx - xx]	x.xx (x.xx - x.xx)	x.xx	x.xx
Dias no hospital (dias)	xx [xx - xx]	xx [xx - xx]	x.xx (x.xx - x.xx)	x.xx	xx [xx - xx]	xx [xx - xx]	x.xx (x.xx - x.xx)	x.xx	x.xx

95%CI - 95% confidence interval; KDIGO - Kidney Disease Improving Global Outcomes; SOFA - Sequential Organ Failure Assessment; ICU - intensive care unit.

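### ICU and hospital length of stay are tested as raw days with no rule for death, so the contrast measures bed use but cannot be read as recovery

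*SAP article*

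**What the plan says.** The SAP, Tertiary outcomes, fixes the model: "Length of stay in the ICU and in the hospital will be compared with mixed generalized linear models", specified as Poisson on the log scale, with site as a random intercept. It says nothing about patients whose stay ends in death. The section opens with the status of these endpoints: "We defined tertiary endpoints that should be considered exploratory".

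The analysis set comes from the general statement in the planned-analysis section: "all analyses will be based on the intention-to-treat principle unless otherwise stated". No exception is made for length of stay. Table 2 has a row beginning "Days in ICU (days" and one for hospital days. Both carry an effect measure with a 95% confidence interval, a p value for each factor and an interaction p value, so these are tested comparisons.

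The Secondary outcomes section does deal with death elsewhere. For ventilator-free days it does so by "assuming zero free-days for those patients who died within that period". For renal replacement therapy it adds a competing-risk model, for acute kidney injury a supportive composite with death, and for total SOFA multiple imputation after death.

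**The concern.** Death ends a stay. On the raw-days scale a death on day 2 scores 2 days and a live discharge on day 8 scores 8, so a lower value has no single clinical meaning. The control group is expected to have 35% mortality at 90 days, so this affects many patients. The Introduction also hypothesises that both interventions reduce mortality, so the trial's own hypothesis can shift length of stay without any change in the speed of recovery. A mortality benefit could then be published beside a longer stay, and readers could take the longer stay as slower recovery. If the handling of death is left until results are known, it becomes the kind of post hoc choice that the SAP says it was written to prevent.

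**Working it through.** **Inputs from the SAP.** 11,000 patients allocated 1:1:1:1, so 5,500 on each side of each factor; 35% control mortality at 90 days; design hazard ratio 0.9; alpha 5% (taken as two-sided).

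**The plan's own figure.** The SAP gives no figure for length of stay. Its power statement, "The defined sample size allowed for an 89% power to detect a hazard ratio of 0.9 for both interventions", checks the inputs borrowed here.
- Risk in the treated arm: 1 − 0.65^0.9 = 0.3214.
- Deaths: 5,500 × (0.35 + 0.3214) = 3,693.
- Schoenfeld: √(3,693/4) × |ln 0.9| − 1.96 = 3.20 − 1.96 = 1.24, which is 89.3% power. The stated 89% reproduces.

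**Illustration for length of stay.** Assume constant hazards of death and of live discharge, with the discharge hazard the same in both arms. Mean stay is 1/(discharge hazard + death hazard). If a fraction f of control patients die in the unit or hospital and treatment multiplies the death hazard by HR, the ratio of mean stays is 1/(1 − f + f × HR). The SAP gives no in-unit or in-hospital death fraction, so f is assumed.
- f = 0.25, HR 0.9: 1/0.975 = 1.026.
- f = 0.35, HR 0.9: 1/0.965 = 1.036. With a mean time to live discharge of 15 days (assumed), that is 9.75 against 10.10 days. The ratio does not depend on the 15.

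**Against sampling error.** If the SD of stay is about equal to its mean (assumed), the SE of the log ratio is √(2/5,500) = 0.019.
- ln 1.026 / 0.0191 = 1.3 SE.
- ln 1.036 / 0.0191 = 1.9 SE.

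In a simulation of the second case (5,500 per arm), the longer stay was significant against the life-saving arm in about 46% of runs with robust standard errors. Plain Poisson standard errors gave about 89%. They also gave about 51% rejections with no difference between arms, so that higher figure largely reflects overdispersion, a separate matter.

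**How firm is the direction?** Now fix the stays instead: survivors stay 15 days, and averted deaths take a survivor's stay. With mortality of 35% against 32.14%, the ratio depends on how long those who die stay:

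| Stay of those who die | Ratio of mean stays |
|---|---|
| 5 days | 1.025 |
| 10 days | 1.011 |
| 15 days | 1.000 |
| 20 days | 0.991 |

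The two set-ups differ in what happens to a patient whose death is averted. In the first the patient stays on and faces the usual discharge hazard. In the second the patient simply acquires a survivor's stay. The sign therefore rests on assumptions that the SAP cannot settle.

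**The case against.** The strongest reply is that little depends on this. The endpoints are exploratory, ICU and hospital mortality are tested in the same section and sit beside length of stay in Table 2, and the primary analysis, sample size and stopping guidelines are untouched. Mean days occupied by all randomised patients is also a legitimate measure of bed use: if more patients survive and occupy beds, the longer stay is real. The SAP never claims that length of stay measures recovery. All of this stands, and it limits the weight of the point.

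Two stronger readings are tempting, and the document does not support either.
- A reader might infer that an arm with more deaths will necessarily look better on length of stay. The fixed-stay check shows that the effect can vanish or reverse. The SAP does not say in words that a death counts as a short stay; this follows from the intention-to-treat default and the absence of any rule.
- A reader might look at a harmful arm and cite a larger distortion. With HR 1.2 and f = 0.35 the ratio is 1/1.07 = 0.935, about 3.5 SE. The same HR with 35% control mortality gives about 1,036 deaths at the 2,750-patient interim if all are followed up, and an expected z for mortality of √(1,036/4) × ln 1.2 = 2.9. That exceeds the charter's P < 0.01 guideline for harm, so length of stay would hardly mislead anyone there.

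The 35% is also 90-day mortality, which can include deaths after discharge, so as an in-hospital fraction it is at the upper end.

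The reply that an article may leave such detail to a fuller document does not stand. The article names the model and the tested rows, and sets death rules for four secondary outcomes. What is fixed here, followed as written, mixes two opposite events.

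**Conclusion.** The point holds in a limited form. As specified, the length-of-stay comparison is interpretable as bed use and not as recovery, and it is out of line with how the plan treats death for its secondary outcomes. At the design effect the artefact is about 2.6% to 3.6% of mean stay, or 1.3 to 1.9 SE, against the better arm. These figures assume an unchanged discharge hazard, constant hazards, 25% to 35% deaths in the unit or hospital, and an SD of stay near its mean. The mixing of death with recovery does not depend on those assumptions; its size and direction do. It is worth correcting because the remedy is cheap, but it does not threaten the trial's main conclusions.

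**What to change.** Make the tested comparison time to discharge alive, from the ICU and from hospital, with death as a competing event. In the constant-hazard illustration with HR 0.9, the proportion eventually discharged alive rises from 65% to 1 − 0.315/0.965 = 67.4% (f = 0.35), or from 75% to 1 − 0.225/0.975 = 76.9% (f = 0.25). The summary then points the same way as mortality.

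An acceptable alternative is ICU-free and hospital-free days within 28 days, with death in the window scored zero, using the rule and model already set for ventilator-free days. Whichever is chosen should be named before the database is unblinded.

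Keep raw days as a description of bed use, overall and by survival status, without a p value.

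The cost is SAP wording and a little more analysis. Live discharge needs only stay dates and vital status, which the planned length-of-stay and mortality outcomes already require. Free days have two further drawbacks: they form a composite that includes mortality, and they need a rule for readmission within the window.

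### ICU and hospital length of stay are fixed to a Poisson model with only a site random intercept, so their intervals and p-values are anti-conservative if stays are overdispersed between patients

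*SAP article*

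**What the plan says.** The Tertiary outcomes section of the SAP article states that length of stay in the ICU and in hospital "will be compared with mixed generalized linear models with a Poisson distribution and a logarithm link", "also considering site as the random intercept effect". For these two outcomes it names no patient-level random effect, dispersion parameter, robust variance, overdispersion check or alternative distribution. The covariates of the primary analysis are specified there for ICU and hospital mortality but not for length of stay. The section opens with "We defined tertiary endpoints that should be considered exploratory".

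Table 2 reserves an effect measure with a 95% CI and a p-value for each of the two margins, plus an interaction p-value, for the length-of-stay rows. The general rule in the section on planned analyses is "An alpha of 5% and 95% confidence intervals will be used unless otherwise stated". Hospital days are summarised in Table 2 as median with interquartile range. The tertiary rows look misaligned in the available text, so nothing is inferred here from the format of the ICU-days row.

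Under Secondary outcomes, by contrast, the SOFA score is to be modelled "using the distribution that best fits the data (Poisson, gamma, inverse gaussian, or multinomial, among others"). Length of stay gets no such latitude.

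**The concern.** The Poisson distribution has one parameter, so the standard error of a rate ratio follows from the mean alone. The observed spread of the data never enters it. The site intercept adds one variance component, for differences between hospitals. Because randomisation is stratified by site, that component largely cancels out of the treatment contrast. Variation between patients within a site, beyond Poisson noise, is left out of the standard error.

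Table 1 lists admission sources from elective surgery to transfer from another ICU, and subgroups that include sepsis and traumatic brain injury. Such patients are unlikely to share one expected length of stay. The median and interquartile range chosen for hospital days also suggest that the authors expect a skewed variable.

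At stake are the intervals and three p-values per length-of-stay outcome in the main outcomes table. A difference in stay that is only noise could be printed there as significant.

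**Working it through.** **The plan's own figures.** The plan states no figure for length of stay. Its one design calculation, 89% power, concerns mortality and does reproduce. Treated mortality is 1 − 0.65^0.9 = 32.1%. Expected events are 5,500 × (0.350 + 0.321) ≈ 3,693. Power is Φ(√3,693/2 × |ln 0.9| − 1.96) = Φ(1.24) = 89%. It does not bear on this point.

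**Inputs.** "BaSICS was designed to enroll 11,000 patients", so there are n = 5,500 per arm on each margin. Alpha is 5%, taken as two-sided. The mean m and standard deviation SD of stay are not in the document, so the values below are assumptions. SD means the spread between patients around the fitted mean.

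**Formulas** for the log ratio of mean stays between two arms of n patients:

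- Poisson model SE = √(2/(n·m))
- Actual SE = √(2·SD²/(n·m²))
- Ratio r = actual/model = √(SD²/m); n cancels
- Actual coverage of the nominal 95% CI = 2Φ(1.96/r) − 1; type I error = 1 − coverage

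**One case in full**, m = 10 and SD = 10. The model SE is √(2/55,000) = 0.0060, an interval of about ±1.2%. The actual SE is √(2/5,500) = 0.0191, about ±3.7%. So r = √10 = 3.16, 1.96/3.16 = 0.62, and the type I error is 2 × (1 − Φ(0.62)) = 54%.

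**Range of assumptions:**

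| Mean / SD (days, assumed) | SD²/mean | CI too narrow by | Actual coverage | Type I error |
|---|---|---|---|---|
| 5 / 2.24 (exactly Poisson) | 1.0 | 1.0 | 95% | 5% |
| 5 / 3 | 1.8 | 1.3 | 86% | 14% |
| 5 / 5 | 5.0 | 2.2 | 62% | 38% |
| 10 / 10 | 10.0 | 3.2 | 46% | 54% |
| 15 / 20 | 26.7 | 5.2 | 30% | 70% |

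**How little overdispersion is tolerable.** A type I error of at most 10% needs 1.96/r ≥ 1.645, so SD²/m ≤ 1.42. For a mean of 10 days that is an SD of at most 3.8.

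**A mild example.** Suppose half the patients have mean stay 4, half have mean stay 10, and each half is exactly Poisson. The pooled mean is 7 and the variance is 7 + 9 = 16. Then r = √(16/7) = 1.5 and the type I error is about 20%, if the model does not include whatever separates the two halves.

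**Simulation check.** Null data were generated for 11,000 patients in 75 sites (assumed), with a site SD of 0.2 on the log mean (assumed), gamma-Poisson stays and 1,000 replicates. Site was fitted as a fixed effect in place of the random intercept. Poisson standard errors gave type I errors of 40% (5/5), 44% (7/7), 56% (10/10) and 68% (15/20), close to the formula. Dispersion-robust standard errors on the same data gave 4.0% to 5.4%, and were 2.3, 2.7, 3.2 and 5.2 times the Poisson ones.

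**The case against.** The strongest objection is that the size is unknown. A reader might infer that the intervals are certain to be several times too narrow and the p-values invalid. The document does not support that, because it contains no mean, SD or variance of stay. At mean 5 and SD 3 the factor is only 1.3. Covariates, if they were added, would also absorb some of the spread between patients. This objection stands, and it is why the point is stated conditionally. It does not remove the mechanism, and nothing elsewhere in the document supplies a dispersion term.

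Second, these outcomes are declared exploratory. They enter no primary or secondary test, no sample-size calculation and no stopping boundary. That also stands and lowers the importance. It does not make a nominal 95% interval cover 95%.

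Third, a reader might infer that the same defect lets an arm with more early deaths show a misleadingly short, seemingly better stay. That is a separate question about the estimand, and a change of variance model would not answer it. The plan does not call a shorter stay better. It reports ICU and hospital mortality beside length of stay, with 90-day mortality as the primary outcome. Stay including patients who died is a legitimate descriptive quantity, and statisticians could differ on whether to add another.

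**Conclusion.** The point holds in conditional form. The plan prescribes a variance assumption that any overdispersion between patients breaks, and it provides nothing to detect or correct this. Over the assumed range, intervals are too narrow by a factor of 1.3 to 5.2, and the type I error is 14% to 70% instead of 5%. The direction is certain once the variance exceeds the mean; the size depends on figures the document does not give. A large trial does not help, because the factor does not depend on the number of patients. The plan's conclusions on its two mortality hypotheses are untouched, so this is something to correct before analysis rather than a threat to the trial.

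**What to change.** In the Tertiary outcomes section, replace the Poisson distribution for ICU and hospital length of stay with a mixed negative-binomial model, keeping the log link and the site random intercept. Alternatively, keep the Poisson mean and state that standard errors will be robust to clustering by site and to overdispersion. Either choice leaves the effect measure a ratio of mean stays, so Table 2 keeps its layout. One of the two should be named before the data are unblinded.

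The cost is one line of SAP wording and a different model call in R. The intervals become wider, which is the correction intended.

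An analysis of time to discharge alive, with death as a competing event, would be an optional separate addition and is not needed to repair this error.
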